## Method/Design

### Study design and setting

We propose a randomized controlled trial with 2 × 2 factorial design in which the two interventions (acupuncture and RehaCom training) are to be delivered to **four** groups defined by the presence or absence of each intervention, with one arm without both interventions as a control group. Patients were randomized to one of the four treatment arms: (i) Experimental Group1 (EG1): conventional treatment plus RehaCom cognitive training; (ii) Experimental Group 2 (EG2): conventional treatment plus acupuncture treatment; (iii) Experimental Group 3 (EG3): conventional treatment plus the combination of acupuncture and RehaCom cognitive training; and (iv) Control Group (CG): Conventional treatment alone. All groups receive the same intervention time of 30 minutes. The investigation will have an intervention period of 12 weeks and will be carried out in the Rehabilitation Hospital Affiliated to Fujian University of Traditional Chinese Medicine (FJTCM). Cognitive abilities screening instrument on cognition performance [includes mini-mental state examination (MMSE), Montreal cognitive assessment (MoCA), functional independence measure scale (FIM)] will be assessed in all groups before and after randomization (at 0,4,8 and 12 weeks). The flow diagram for this trial is presented in Figure 1.

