**Flow diagram of participants.**

### Sample size

We use the improvement of MMSE scores as the main effect indicators to estimate the sample size. Sample size calculations are performed to determine the number of participants needed to detect effect sizes. Based on the similar papers reported before [38–40] and our preliminary data indicates the mean with SD of the MMSE scores were μ1 = 2.7, μ2 = 5.9, μ3 = 3.7, μ4 = 6 in the CG, EG1, EG2, EG3 respectively, with the SD *σ* = 5.2. To detect 4.6 mean differences among the groups at end of interventions, k represents of the number of groups which is 4 in this trial. About 50 individuals per group will be calculated according to the formula:

With a type I error of 5% (α = 0.05) and 90% power (β = 0.10). Estimating a 20% dropout rate during the study, a minimum of 240 total participants is needed to reach the target 60 participants per group.

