### Outcome assessment

This study will run for 12 weeks and cognitive function will be assessed by neuropsychological measurement scales which include Mini–mental state examination (MMSE), Montreal Cognitive Assessment (MoCA), Functional Independence Measure Scale (FIM) at baseline and again at 4, 8 and 12 weeks (within a time window: +/- 3 days). All outcomes will be measured by several experienced assessors who are blinded to the randomization group after the baseline visit in the Evaluation Department of Rehabilitation Hospital Affiliated to FJTCM.

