### Statistical analysis

All allocated subjects will be analyzed with the available data, i.e. on the basis of the intention-to-treat (ITT). A significance level of 95% (two sided p-values alpha < 0.05) will be used. After examining the data for normality (Kolmogorov-Smirnov test) the outcome measures will be analyzed using ANOVA (assuming normal distribution) or Kruskal-Wallis (non-parametric). Demographic characteristics and other baseline values will be described using descriptive statistics for each group. Significant group interactions will be analyzed post-hoc. We will use the Bonferroni method to appropriately adjust the overall level of significance for multiple outcomes.

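### The planned ANOVA is unadjusted and its response variable is not fixed; a factorial ANCOVA on the baseline score would be a cheap gain in precision, of a size the article cannot settle

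*Protocol article*

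**What the plan says.** On measurement, the Study design and setting section states that MMSE, MoCA and FIM "will be assessed in all groups before and after randomization (at 0,4,8 and 12 weeks", and the Outcome assessment section repeats the schedule: "at baseline and again at 4, 8 and 12 weeks".

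On analysis, the Statistical analysis section states that "the outcome measures will be analyzed using ANOVA (assuming normal distribution) or Kruskal-Wallis (non-parametric" and then that "Demographic characteristics and other baseline values will be described using descriptive statistics for each group". No covariate is named there or elsewhere, and the section does not say whether the outcome measures enter as week-12 scores, as changes or as repeated visits.

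On planning, the Sample size section states: "We use the improvement of MMSE scores as the main effect indicators to estimate the sample size". It gives "μ1 = 2.7, μ2 = 5.9, μ3 = 3.7, μ4 = 6 in the CG, EG1, EG2, EG3 respectively", "with the SD *σ* = 5.2", and later adds "To detect 4.6 mean differences among the groups at end of interventions".

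**The concern.** Two things are left in a poor state.

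First, the response variable of the primary analysis is open. Planning is on improvement, the same section then speaks of differences at the end of the interventions, and the analysis section settles neither. Week-12 scores and changes have different variances and react in opposite directions to a chance difference between arms at baseline.

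Second, whichever is meant, the named method does not estimate the relation between baseline and outcome. A week-12 ANOVA sets the baseline slope to 0 and a change-score ANOVA sets it to 1. Patients enter because their MMSE is low, so some regression to the mean is expected and a slope below 1 is plausible: an arm that starts lower by chance then tends to gain more. ANCOVA estimates the slope from data that are already collected. At stake are precision and protection against chance imbalance. The validity of the randomised comparison is not in question.

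**Working it through.** **Inputs.** From the Sample size section: planning means 2.7 (CG), 5.9 (EG1), 3.7 (EG2) and 6.0 (EG3); SD 5.2; power 90%; about 50 per arm before dropout and 60 after. From the Statistical analysis section: two-sided 5%. The baseline-to-week-12 correlation r is not given and is taken as 0.3 to 0.8 (assumption). The baseline SD is not given either. The stated difference of 4.6 is not used, because it matches no gap between two planning means (the largest is 6.0 − 2.7 = 3.3).

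**Step 1: the plan's own figure.** The grand mean is 18.3/4 = 4.575. The sum of squared deviations is 3.516 + 1.756 + 0.766 + 2.031 = 8.0675. For a four-group ANOVA the noncentrality is n × 8.0675/5.2², which is 14.9 at n = 50. The noncentral F distribution gives 49 per arm for 90% power, and 91.0% power at 50. The stated figure reproduces without any adjustment. With 20% lost from 60, 48 per arm remain and power is 89.7%.

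**Step 2: which variable is it?** Means of 2.7 to 6.0 on a 30-point scale make sense only as changes. For MMSE, then, baseline probably enters by subtraction. For MoCA and FIM the article gives no such pointer.

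**Step 3: variance factors with equal SDs at baseline and week 12 (assumption).** ANCOVA variance is (1 + r)/2 of change-score ANOVA and 1 − r² of week-12 ANOVA. The first comparison takes 5.2 as the SD of change, the second as the SD of the week-12 score.

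| r (assumed) | vs change | n per arm, 90% power | power at 50 per arm | vs week-12 score | n per arm, 90% power |
|---|---|---|---|---|---|
| 0.3 | 0.65 | 32 | 98.7% | 0.91 | 45 |
| 0.5 | 0.75 | 37 | 97.2% | 0.75 | 37 |
| 0.7 | 0.85 | 42 | 95.0% | 0.51 | 26 |
| 0.8 | 0.90 | 44 | 93.8% | 0.36 | 19 |

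Against change scores the variance saved is 10% (r = 0.8) to 35% (r = 0.3).

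**Step 4: unequal SDs.** Let k be the baseline SD divided by the week-12 SD. The ratio of ANCOVA to change-score variance is (1 − r²)/(1 + k² − 2rk). For an assumed k = 0.8:
- r = 0.5: 0.75/0.84 = 0.893, a saving of 11%.
- r = 0.7: 0.51/0.52 = 0.981, a saving of 2%.
- k = r: the true slope is r/k = 1, and the saving is nil.

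The entry ceilings on MMSE make k below 1 plausible. If k exceeds 1, the saving can be larger than in Step 3.

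**Step 5: chance imbalance.** The change-score contrast differs from the adjusted contrast by (1 − slope) × the baseline difference. With equal SDs and r = 0.5 the slope is 0.5, so an arm that starts 1 point lower by chance is favoured by (1 − 0.5) × 1 = 0.5 points in a change-score ANOVA.

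**Step 6: main effects and interaction.** At 50 per arm the main-effect SE is 5.2 × √(2/100) = 0.735 and the interaction SE is 5.2 × √(4/50) = 1.471. Adjustment multiplies both by the same factor: at r = 0.5, √0.75 = 0.866 gives 0.637 and 1.274. The interaction detectable with 90% power is 3.2415 × 1.471 = 4.8 points unadjusted. Against change scores with equal SDs it becomes 3.8 (r = 0.3) to 4.5 (r = 0.8). The planning means imply an interaction of 6.0 − 5.9 − 3.7 + 2.7 = −0.9. Power for that value is 9.3% unadjusted and 9.8% to 13.7% adjusted, over r = 0.3 to 0.7 and both readings of the SD.

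**The case against.** The best defence has four parts.

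- The sentence on describing baseline values is the usual baseline-table statement. It does not exclude a covariate, and a condensed article may leave covariates to the analysis plan. This stands in part: adjustment is not ruled out. But the article does name a method, and that method is unadjusted.
- A reader might infer that baseline scores serve for description only, and hence that the full 1 − r² loss applies, which is 25% to 49% at r = 0.5 to 0.7. The documents do not support this for MMSE, because the sample size is built on improvement. The larger loss applies only if week-12 scores are analysed.
- A reader might also take the education-specific cut-offs and mixed recruitment as proof of a wide baseline spread. No baseline SD is given, and the cut-offs are ceilings that truncate the range within each education group.
- Unadjusted ANOVA is valid under randomisation, and the plan reaches its 90% power without adjustment. Both statements are right, which makes this a point about efficiency and clarity.

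Against all four, linear baseline adjustment is in large samples never less efficient than either unadjusted analysis, and it costs about one degree of freedom.

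**Conclusion.** The point holds as a cheap improvement and a clarification. The article names an unadjusted analysis, leaves open whether it applies to change or to week-12 score, and states no use of baseline MoCA or FIM beyond description.

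The gain over a change-score ANOVA is 10% to 35% of variance for an assumed r of 0.8 to 0.3 with equal SDs, and may be near zero if the baseline SD is smaller. Since neither r nor the baseline SD is reported, no single figure should be claimed.

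Three stronger conclusions do not follow. The sample size is not wrong on this account. The interaction is not penalised more than the main effects: its SE is double by design, and the proportional loss is the same for every contrast. Nor does adjustment make the synergy test adequate, since the detectable interaction stays far above the 0.9 points in size that the planning means imply.

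**What to change.** Replace the unadjusted ANOVA by one sentence: the primary analysis is a 2×2 factorial linear model (ANCOVA) of the week-12 MMSE score, with terms for acupuncture, RehaCom training and their interaction, and baseline MMSE as covariate; MoCA and FIM are analysed in the same way with their own baseline scores. The education group used for eligibility may be added as a further covariate, but this is optional and nothing in the article allows its benefit to be sized. If a rank-based fallback is kept, label it a sensitivity analysis, since Kruskal-Wallis takes no covariate.

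The data are already collected, no patients are added, and the cost is about one degree of freedom per model. The change should be made before the allocation code is opened.

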In this trial, our first aim is to evaluate the synergistic effect of acupuncture and RehaCom cognitive training on cognitive dysfunction after stroke. Our second aim is to determine whether acupuncture and RehaCom cognitive training, alone or in combination, are more effective than conventional treatment on the rehabilitation of post-stroke cognitive dysfunction. The work reported in this article is financed by the Program of International S&T Cooperation (No. 2011DFG33240), Ministry of Science and Technology of the People’s Republic of China.

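### The Bonferroni rule for multiple outcomes does not say whether MMSE keeps the alpha of 0.05 on which the trial was sized

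*Protocol article*

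**What the plan says.** Under Sample size, the calculation rests on one outcome: "We use the improvement of MMSE scores as the main effect indicators to estimate the sample size". The error rates are given as "With a type I error of 5% (α = 0.05) and 90% power (β = 0.10", with no adjustment of alpha. The result is about 50 per group, raised to 60 per group (240 in total) for 20% dropout.

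Under Primary outcomes, MMSE is the only measure listed. MoCA and FIM stand under Secondary outcomes.

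Under Statistical analysis there are two statements on the level of the tests. The first is "A significance level of 95% (two sided p-values alpha < 0.05) will be used". The second is "We will use the Bonferroni method to appropriately adjust the overall level of significance for multiple outcomes". The number of outcomes in the family is not given, and nothing says whether MMSE belongs to it.

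The second aim, at the end of the Background, is whether the two interventions, "alone or in combination, are more effective than conventional treatment on the rehabilitation of post-stroke cognitive dysfunction". That implies at least three comparisons with the control group. On comparisons between groups, the Statistical analysis section says only that significant group interactions will be followed up post hoc. It names no method of adjustment for them.

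**The concern.** Taken at its word, a correction for multiple outcomes covers the outcome measures, and the article lists MMSE, MoCA and FIM together as such. MMSE would then be tested at 0.05/3 = 0.0167, a level for which the trial was not sized. The stated 90% power would no longer describe the primary test.

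The decision rule is also at stake. An MMSE p-value between 0.0167 and 0.05 would be a positive result if MMSE stands outside the family and a negative one if it is one of three outcomes inside it. The level for a sole primary outcome should not depend on which of two published sentences is followed.

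**Working it through.** **Inputs, all from Sample size.** Mean improvements: "μ1 = 2.7, μ2 = 5.9, μ3 = 3.7, μ4 = 6 in the CG, EG1, EG2, EG3 respectively". Spread: "with the SD *σ* = 5.2". Groups: "k represents of the number of groups which is 4 in this trial". Completers per arm: 50 as stated, or 60 × 0.8 = 48 if 20% of the 60 randomised per arm drop out.

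**Method.** One-way ANOVA F test, power from the noncentral F distribution with 3 and 4(n − 1) degrees of freedom and noncentrality λ = n × Σ(μi − mean)² / σ².

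- Grand mean: (2.7 + 5.9 + 3.7 + 6.0)/4 = 4.575.
- Sum of squares: 1.875² + 1.325² + 0.875² + 1.425² = 8.0675.
- λ = n × 8.0675/27.04, that is 14.92 at n = 50 and 14.32 at n = 48.

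**The plan's own figure.** At alpha 0.05 the smallest n with 90% power is 49 per arm, against the stated figure of about 50. The omnibus F test is therefore a fair benchmark for what the stated power means.

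**Power of that test under each reading of the rule.** The divisor is an assumption, because the article gives none.

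| Reading | Alpha for MMSE | 50 per arm | 48 per arm |
|---|---|---|---|
| Bonferroni on MoCA and FIM only | 0.05 | 91.0% | 89.7% |
| MMSE one of two outcomes | 0.025 | 85.4% | 83.6% |
| MMSE one of three outcomes | 0.0167 | 81.7% | 79.6% |

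To keep 90% power at 0.05/3, 61 completers per arm are needed. With 20% dropout that is 61/0.8 = 76.25, so 77 per arm or 308 in total, against the planned 240.

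**Comparisons with control.** With 50 per arm and no true differences (simulation, 400,000 draws), three comparisons with control at 0.05 each give at least one false positive in 12.5% of trials if tested without a gate. If they are tested only after a significant omnibus F test, the figure is 4.0%. If one active arm truly differs from control by 3.2 or more, the gate is usually open, and the chance of a false positive on the other two comparisons is about 9%.

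**Cost of adjusting those comparisons**, on the planning means with 50 per arm:

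| Comparison | Unadjusted 0.05 | Dunnett | Holm |
|---|---|---|---|
| EG1 vs CG | 86% | 76% | 78% |
| EG3 vs CG | 88% | 79% | 80% |

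That is a loss of about 8 to 10 points for each of these two comparisons.

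**The case against.** The strongest reply is that the text can be read consistently. MMSE is the sole primary outcome, the section sets a two-sided level of 0.05, and Bonferroni can be taken to apply to the secondary scales. On that reading MMSE keeps 0.05 and no power is lost. This stands as a possible reading. A reader might infer that the article contradicts itself and that power falls to about 80%. The wording does not go that far, because both the inclusion of MMSE and a divisor of three have to be assumed. Equally, nothing in the text exempts MMSE, so the favourable reading is also an assumption.

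A second tempting inference is that false-positive control is absent for the comparisons with control. The article does not say these will be unadjusted. It names no method, and a condensed article may leave that to the analysis plan. The planned ANOVA followed by post-hoc work can also be read as a gate, although its wording refers to interactions rather than to comparisons with control. What remains is modest: an omnibus gate controls the error when no arm differs but only weakly once one does, and the planning means assume that EG1 and EG3 do.

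A third objection is that omnibus power does not describe the first aim, synergy, which is an interaction. That is correct. The figures here speak only to the test for which the article states its power.

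**Conclusion.** The mismatch holds. The trial is sized for MMSE at an unadjusted 0.05, while the analysis text announces a correction over outcomes without saying whether MMSE is exempt. On the planning means and SD, with 48 to 50 completers per arm, omnibus power lies between about 80% and 91%: 90% to 91% if MMSE stands outside the family, 84% to 85% if it shares alpha with one other outcome, and 80% to 82% if it shares alpha with two. The lower figures depend on an assumed divisor.

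This is an ambiguity in the level of the primary test, with a possible loss of up to about 10 points of power. It is not a proven error in the sample size, and it does not show that the comparisons with control are uncontrolled.

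**What to change.** State in the Statistical analysis section that MMSE at week 12, the single primary outcome, is tested at two-sided 0.05 outside the Bonferroni family, and that Bonferroni or Holm applies only to MoCA and FIM as secondary outcomes. This takes one or two sentences and no extra patients, and it keeps the stated power. The price is that a result on MoCA or FIM alone cannot make the trial positive.

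If the sponsor prefers Bonferroni over all three outcomes, the Sample size section should give the power as about 80%, or the trial should be enlarged as shown in the working.

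If the three comparisons with control on MMSE are to support separate claims, name the method of control. Dunnett or Holm would do, at the cost in power per comparison shown above, and that cost should be stated rather than treated as negligible.

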### Quality control

A trained RA will explain to each participant the nature of the study, its purpose, the procedures involved, the expected duration, the potential risks and benefits and any discomfort it may entail. Patients or their legal guardians will receive an information letter about the study and there will be no time limit for them to consider implications, ask questions, and respond to the invitation to participate. Participants will be informed that they are free to withdraw from the treatment under study at any stage for any reason without any consequences.The participants screening must according to the inclusion and exclusion criteria. If they meet the inclusion criteria and not meet the exclusion criteria, this procedure will pass. On the contrary, the disqualified participants will be excluded, and the researchers will record the number and the reasons.The random allocation sequence will be produced by an independent statistician via the statistical software SAS 9.1. The project manager allocates the participants according to the random allocation sequence, and it must be deposited for safe keeping ensuring nobody else knows. The cessation of blinding will take place only after all the trial is completed.The missing data should not appear in the CRFs of the missing data in principle. If any missing data appears, researchers should find out whether it is missed in the raw data. If it is missed when loading into database, it should be reloaded. If the missing data affects outcome measure, the participant will be rejected.To ensure that treatments are of a high standard and delivered in accordance with the trial protocol, clinicians involved in assessments, treatment or training will have to provide proven record of at least three year of clinical experience and certified training or education in related fields of rehabilitation or research. The needling will only be performed by professional physicians with specific training in TCM and a minimum of five years of experience. They will participate in a two-day training in the standard operating procedures (SOPs) provided by the author of the manualized protocol and the standard operation videos. In this training the protocol will be explained and practiced on each other during exercises and role-plays. The therapist in the control condition will receive no extra training. In addition, all treatments provided to patients will be carefully recorded in the CRFs.Blinding of study personnel in research projects is a main quality criterion of a study [43]. Although patients, investigators, and therapists administering treatment will not be blinded, those assessing the patients for primary and secondary endpoints will be blinded to patient treatment assignment. The investigators, therapists and assessors are different people. Patients will be told not to talk to the examiner about the group allocation or therapy content during the post-intervention assessments.To maintain the quality of this trial, monitoring will be conducted by the PL located in the Rehabilitation Hospital Affiliated to FJTCM. Investigators can also be convened to discuss practical issues that might be encountered, such as dealing with serious adverse events, revising the protocol, and addressing certain important issues that might be raised by investigators and participants.

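### The rule that rejects participants with missing outcome data contradicts the stated intention-to-treat analysis and, applied as written, removes randomised participants together with their week 4 and week 8 MMSE

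*Protocol article*

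**What the plan says.** Two sections of the protocol article set the rule for incomplete outcomes.

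- **Statistical analysis:** "All allocated subjects will be analyzed with the available data, i.e. on the basis of the intention-to-treat (ITT".
- **Quality control:** a gap that arose at data entry is repaired ("If it is missed when loading into database, it should be reloaded"). The next step, for what remains, is "If the missing data affects outcome measure, the participant will be rejected".

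No section limits the rejection to a per-protocol or secondary analysis set.

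Three other statements bear on how often the rule could apply. Outcomes are measured "at baseline and again at 4, 8 and 12 weeks" (Outcome assessment). The sample size allows for loss: "Estimating a 20% dropout rate during the study" (Sample size). Patients are not blinded (Blinding) and are told that "they are free to withdraw from the treatment under study at any stage for any reason without any consequences" (Quality control).

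**The concern.** A participant seen at baseline, week 4 and week 8 but not at week 12 is kept by one rule and removed by the other. An analyst cannot follow both. If the choice is left open, it may be made after the data are seen, or a result in participants with complete outcomes may be reported as intention-to-treat.

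Exclusion after randomisation gives up the protection that randomisation provides. Removing the whole participant also discards the week 4 and week 8 MMSE, which are the data that could correct for dropout related to earlier response. Patients know their allocation in this trial, so loss that is related to arm or response is plausible, although the protocol gives no figures by arm.

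**Working it through.** **1. The two rules applied to the same participant**

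| Participant | Statistical analysis section | Quality control section |
|---|---|---|
| All visits present | kept | kept |
| Entry error, source data exist | kept | kept after reloading |
| Weeks 4 and 8 present, week 12 missing | kept, with weeks 4 and 8 | removed entirely |
| No post-baseline MMSE | kept in name, contributes no outcome | removed |

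The rules differ in practice in the third row, that is, for partial data.

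**2. The plan's own sample size**

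Inputs (Sample size section): mean MMSE improvement 2.7 (CG), 5.9 (EG1), 3.7 (EG2) and 6 (EG3); SD 5.2; alpha 0.05; power 90%.

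- Grand mean = (2.7 + 5.9 + 3.7 + 6)/4 = 4.575.
- Sum of squared deviations = 3.516 + 1.756 + 0.766 + 2.031 = 8.07 (rounded).
- Cohen's f = √(8.0675/4)/5.2 = 0.273.
- One-way ANOVA with four groups (noncentral F) needs 49 per group. The plan's figure of about 50 reproduces.
- The planned 60 per group follows from 48/(1 − 0.2) = 60, or from 50 × 1.2 = 60.

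**3. What the rejection rule removes at the planned dropout**

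- 240 × 0.20 = 48 participants, or 12 per group if loss is equal.
- 240 − 48 = 192 remain, or 48 per group.
- ANOVA power is 89.7% at 48 per group, 91.0% at 50, and 95.5% at 60 (only if all 240 give full data).

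The planned power is essentially intact at 48 per group.

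**4. Size of a possible bias (assumed scenarios; the documents give none of these inputs except 20% and SD 5.2)**

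*Loss that differs by arm.* Let retained participants in each arm improve by g points more than rejected ones, and let d be the fraction lost. The mean in retained participants exceeds the mean in all participants by d × g. The difference between two arms is then off by (d₁ − d₂) × g.

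- Equal loss and equal g: 0.
- Loss of 30% against 10%, g from 1 to 5.2: 0.2 × 1 = 0.2 to 0.2 × 5.2 = 1.04 points.

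*Response-related loss in one arm only, random loss in the comparator.* Assume that the log-odds of dropout rise by b for each SD of worse week-8 response, that overall loss is 20%, and that the correlation of week 8 with week 12 is ρ. The shift in the week-12 mean of retained participants is ρ × 5.2 × E(z | retained), where z is the standardised week-8 response.

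| b | E(z given retained) | Shift, ρ = 0.8 | Shift, ρ = 0.5 |
|---|---|---|---|
| 0.5 | 0.096 | 0.40 | 0.25 |
| 1.0 | 0.173 | 0.72 | 0.45 |
| 1.5 | 0.227 | 0.94 | 0.59 |

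In the extreme case, the lowest 20% on week-8 response all leave. Then E(z | retained) = φ(0.842)/0.8 = 0.280/0.8 = 0.350, and the shift at ρ = 0.8 is 0.8 × 5.2 × 0.350 = 1.46.

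**5. Yardsticks from the plan's means**

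- Acupuncture minus control: 3.7 − 2.7 = 1.0.
- RehaCom minus control: 5.9 − 2.7 = 3.2.
- Combination minus control: 6 − 2.7 = 3.3.

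**The case against.** Four points can fairly be made in defence of the plan.

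**The rejection sentence is not the only cause of loss.** The plan names ANOVA or Kruskal-Wallis on available data, and sizes the trial on differences at the end of the intervention. An available-case comparison at week 12 omits anyone without week-12 MMSE whether or not the rejection sentence exists. This stands. A reader might infer that the sentence alone turns the primary analysis into a completers analysis. The documents do not support that, and deleting it alone would not recover these participants at week 12.

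**The sentence is loosely worded.** It sits among instructions on case report forms and database entry, and neither the rejection nor the kind of outcome affected is defined. Table 1 records dropouts and withdrawals as a separate item, and freedom to stop treatment need not mean missed assessments. So 48 is an upper figure at the planned dropout rate. The narrow reading, a discarded form or an entry error, does not hold, because entry errors are dealt with in the preceding sentence and it is the participant who is rejected.

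**Unequal burden is not established.** A reader might infer from Table 2 that three arms carry extra sessions and control none, so that dropout must differ. Study design and setting, however, gives all groups the same 30-minute intervention time. Differential dropout is therefore a possibility and not a documented fact.

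**The bias figures are scenarios.** They need selection in one arm only and an assumed correlation, and the 1.0-point yardstick is the smallest planned contrast with control. A reader might infer that the bias would match the effects under test. The other two contrasts with control, 3.2 and 3.3, are well above every illustrated figure. Nor should 1.8 points (5.2 × 0.350 = 1.82) be taken as the worst case for loss driven by week-8 response at a correlation of 0.8. It requires dropout to depend on the week-12 value itself.

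**Conclusion.** The contradiction is real and lies in the stated text, so it is not a detail left to an analysis plan. If the Quality control rule is followed as written, randomised participants with partial outcomes are removed and the analysis is not intention-to-treat. Up to 48 of 240 could be affected at the planned 20% dropout.

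Power is not the reason to act. The reason is the risk of bias if loss differs by arm or depends on response. The documents do not determine its size, and it is zero when loss and mechanism are equal across arms. Under the assumed one-arm scenario with a correlation of 0.8 it is about 0.4 to 0.9 MMSE points, and up to about 1.5 in the extreme case. That is material for the acupuncture-control difference of 1.0 and less so for the larger contrasts. Part of this risk comes from an available-case week-12 ANOVA and would remain if only the sentence were removed.

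**What to change.** 1. Delete the rejection sentence, or confine it to a per-protocol sensitivity set that is named as such.
2. State that every randomised participant stays in the analysis in the allocated arm.
3. Analyse MMSE at weeks 4, 8 and 12 with a method valid under missing at random, so that participants without week 12 still contribute. One suitable choice is a likelihood-based repeated-measures model with baseline MMSE, visit, acupuncture, RehaCom and their interaction, with week 12 primary. Other methods valid under the same assumption would also serve.
4. Add one sensitivity analysis for data not missing at random, for example a delta adjustment for participants who drop out.

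The first two steps are wording changes. The last two cost slightly more analysis work on data that are already scheduled. The article reports recruitment as ongoing, so the change should be made before the allocation code is opened.
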